### Cost-effectiveness

Incremental costs effectiveness ratio (ICER) will be calculated and expressed as (a) the cost per woman that displays a significantly reduced level of FoC, and (b) the cost per QALY. Standard sensitivity analyses will be performed to test for the robustness of the cost-effectiveness result. Non-parametric bootstrapping method will be used, performing 1000 replications of the original costs data, to produce confidence intervals around the costs estimates and quantify uncertainty around the calculated ICERs [85]. Cost-effectiveness planes will be used to represent the bootstrapped ICERs: the horizontal line reflects the difference in effect and the vertical line reflects the difference in costs. Cost-effectiveness acceptability curves will be used to inform decision-makers on the probability that the studied intervention is cost-effective at a range of ceiling ratios.

### Dissemination recommendation

In order to inform future dissemination of MBCP into midwifery care we will evaluate the value of MBCP for midwifery care taking into account clinical relevance. Two pillars will provide perspective on clinical relevance: (I) the clinical significance of the effects and (II) acceptability and feasibility of MBCP for the participants. To assess the clinical significance of MBCP, we will compare the pre- and post-treatment raw scores of primary and secondary measures with current established norms relevant for a population of pregnant women. To assess acceptability and feasibility of MBCP, participants will be asked to complete an evaluation form about the personal value they found from participating in the program, along with our assessment of the number of sessions attended and adherence to home practice.

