## Background

Fear of childbirth (FoC) is a highly prevalent negative emotion among pregnant women characterized by high levels of stress and emotional maladaptation to the normal physiological and psychological processes of being pregnant and giving birth [1, 2]. Reports demonstrate that approximately 25 % of pregnant women suffer from a high level of FoC, as assessed by the Wijma Delivery Expectancy/Experience Questionnaire (W-DEQ-A and B), defined as a W-DEQ-A score ≥66 [3]. Besides, approximately 10 % of pregnant women have been found to suffer from severe FoC (W-DEQ-A score ≥85) [4]. The complex causes of FoC can be examined from a biopsychosocial perspective [5] that includes biologically-oriented dimensions of fear (e.g., fear of pain, fear of bodily harm, or fear of one’s own or one’s infant’s death), psychological factors (e.g., personality traits, a history of traumatic life events or previous difficult or traumatic obstetrical experiences, feelings of helplessness, or anxiety about motherhood), and social factors (e.g., dissatisfaction with the partner relationship, lack of social support, low socioeconomic status, hearing ‘horror stories’ about labour from family, friends, acquaintances, and media sources) [1, 6, 7]. FoC can be categorized as ‘primary FoC’ occurring in nulliparous women (first-time mothers) and ‘secondary FoC’ following a previous difficult or traumatic childbirth experience. Differences in severity of FoC between nulliparous and parous women are still being investigated [8, 9]. FoC seems to be a specific domain of anxiety associated with, yet distinct from, general anxiety or depression [10]. Only a small number of studies have evaluated the content and interrelationship of pregnant women’s FoC and their partners’ FoC [11, 12]; the role of fathers’ perinatal distress as a contributing factor to FoC among pregnant women is still unknown.

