## Methods

### Design

The study design is a quasi-experimental controlled trial with two arms (intervention and active comparison group) involving four assessment time points. Participants will be allocated by the order of inclusion in the study (alternation). Inclusion will take place at baseline 16–26 weeks gestational age. Subsequently, questionnaires will be filled in one-two weeks pre-intervention (T1) and post-intervention (T2), and two-four weeks (T3) and 16–20 weeks (T4) following the birth. Participating couples will receive a fee of €50 upon completion of data collection (T4).

Participants from an urban area in The Netherlands will be quasi-randomized to the intervention (MBCP) or comparison group (FoCC) using an Excel program of created codes with the intent of producing equivalent training group cohorts of approximately six participants each. The flowchart of the study design and participants is depicted in Fig. 2.

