### Recruitment

Figure 2 provides an overview of the recruitment and study procedures. Recruitment for this study started in April 2014. Midwives and obstetricians were briefed on the study at workshops and fraternity meetings. Pregnant women are invited to join the study in two ways: via advertisement posters and brochures in midwifery waiting rooms inviting them to visit the study’s website http://www.mbcpmidwife.nl/ or by midwives and obstetricians who find they are caring for a highly anxious and/or stressed pregnant woman and offer them information about the study. After a potentially eligible pregnant woman or her care provider contacts the research team, informed consent is obtained. Subsequently, the pregnant woman completes an online screening questionnaire (W-DEQ-A) [3]. Questionnaire responses are scored within 48 h. Women who score ≥66 on the W-DEQ-A are contacted by telephone and the study’s two-stage exclusion protocol is administered. After this procedure, the eligible participant’s partner is invited to join the study, informed consent is obtained and the two-step exclusion interview is administered.

The first step of the exclusion protocol is carried out by the research midwife by telephone in order to identify a current risk for a psychosis/psychotic disorder, potential suicidal risk, substance abuse and dependency, or borderline personality disorder in the woman and/or her partner. In cases where any of the above risks or disorders are suspected, an extensive personal psychological interview is conducted by a trained psychologist using the Structured Clinical Interview for DSM-IV disorders Axis I and Axis II (SCID-I and SCID-II) [64]. Subsequently the general physician of the participant is informed of the existing or risk for a particular mental disorder.

Recruitment will continue until at least 64 participants with a W-DEQ-A score ≥66 have completed the study’s programme in each of two study arms.

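### The clinical significance of MBCP is to be read from pre- and post-treatment scores against norms with no FoCC contrast, so change that would occur anyway can count as benefit

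*Protocol article*

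**What the plan says.** The Dissemination recommendation section sets out how MBCP's value for midwifery care will be judged: "Two pillars will provide perspective on clinical relevance: (I) the clinical significance of the effects and (II) acceptability and feasibility of MBCP for the participants". For the first pillar, the clinical significance of MBCP, the method is given: "we will compare the pre- and post-treatment raw scores of primary and secondary measures with current established norms". The norms are those for pregnant women. No arm is named for the scores and no contrast with FoCC is mentioned. The second pillar rests on an evaluation form, sessions attended and home practice, and it has no comparator either.

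Entry depends on a high score on one of the outcome scales. Under Recruitment, "Women who score ≥66 on the W-DEQ-A are contacted by telephone" and go on to the exclusion interview. The Background reports that "approximately 25 % of pregnant women suffer from a high level of FoC", meaning 66 or more on W-DEQ-A.

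A concurrent control exists. The Design section describes "two arms (intervention and active comparison group) involving four assessment time points", and Table 4 schedules W-DEQ-A at T1 and T2. Under Primary analyses, efficacy is tested by the time-by-condition interaction. The dissemination section does not carry that contrast over.

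**The concern.** A change from before to after treatment mixes the effect of MBCP with everything else that happens in the same weeks. Here that includes:

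- advancing pregnancy over a nine-week programme;
- concurrent care, since the exclusion criteria allow ongoing psychological treatment and prenatal courses;
- the attention that any structured programme brings.

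A population norm as benchmark removes none of these. Only the FoCC arm, measured on the same schedule, can do so. FoCC is itself active care whose effect the protocol calls unknown, so movement towards the norm under MBCP does not show that MBCP adds anything to it.

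Selection on a high W-DEQ-A score raises a second question, namely how much of the movement towards the norm would be regression to the mean.

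At stake is the clinical half of the conclusion. The Discussion ties the study's importance to benefits that are both statistically and clinically meaningful. As written, the statistical part is controlled and the clinical part is not.

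**Working it through.** The dissemination section prints no figure that could be reproduced. The argument about natural change is a reading of the text and needs no arithmetic. The arithmetic below sizes only the regression component, assuming no treatment effect and no natural change.

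**Inputs from the Background.** 25 % of pregnant women score 66 or more. For the severe level, "approximately 10 % of pregnant women have been found to suffer from severe FoC (W-DEQ-A score ≥85").

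**Assumptions.** Scores are normal, the trial draws on the top 25 % of such a population, T1 is the pre score and T2 the post score. The correlations between occasions are not in the document, so a range is shown.

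**Step 1: implied scale.**
- SD = (85 − 66) / (1.2816 − 0.6745) = 31.3 points.
- Mean = 66 − 0.6745 × 31.3 = 44.9.
- Mean of the selected women, in SD units above the population mean: φ(0.6745) / 0.25 = 1.271. This is 44.9 + 1.271 × 31.3 = 84.7 points.

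**Step 2: screening to T1.** T1 is a separate measurement after screening. The expected fall to it is 1.271 × (1 − r) SD. At r = 0.9 this is 0.13 SD (4.0 points), and at r = 0.5 it is 0.64 SD (19.9 points). If T1 is the pre score, this fall has already happened and does not enter the T1-to-T2 change.

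**Step 3: T1 to T2.** With r(S,T1) and r(S,T2) the correlations of the screening score with T1 and T2:

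fall in mean = 1.271 × [r(S,T1) − r(S,T2)] SD

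*Constant correlation.* The bracket is zero, so the mean does not fall.

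| r, all occasions | Share of women at or above 66 at T1 who are below 66 at T2 | Whole arm: moves down | Whole arm: moves up | Share below 66, T1 to T2 |
|---|---|---|---|---|
| 0.9 | 13 % | 10.2 % | 10.2 % | 23 % to 23 % |
| 0.8 | 20 % | 13.6 % | 13.6 % | 32 % to 32 % |
| 0.7 | 26 % | 15.9 % | 15.9 % | 40 % to 40 % |

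Downward crossings are fully offset by upward ones, so there is no net artefact.

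*Decaying correlation (first-order autoregressive).* Then r(S,T2) = r(S,T1) × r(T1,T2).

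| r(S,T1), r(T1,T2) | r(S,T2) | Fall in mean | In points (× 31.3) | Share below 66, T1 to T2 |
|---|---|---|---|---|
| 0.9, 0.8 | 0.72 | 1.271 × 0.18 = 0.23 SD | 7.2 | 23 % to 38 % |
| 0.9, 0.7 | 0.63 | 1.271 × 0.27 = 0.34 SD | 10.7 | 23 % to 44 % |

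**Step 4: less extreme selection.** Recruitment runs through posters and through caregivers who notice anxious or stressed women, so the source pool may score higher than pregnant women at large. If 50 % of the pool scored 66 or more, the multiplier 1.271 becomes 0.798 and the fall is 0.14 to 0.22 SD of that pool. At 70 % it becomes 0.497 and the fall is 0.09 to 0.13 SD.

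**Step 5: the same in FoCC.** Both arms enter through the same screen and are measured at the same occasions. Under these assumptions the expected fall is equal in both, and the between-arm difference is zero.

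**The case against.** The strongest reply is that one condensed sentence in a journal article does not exclude FoCC. It does not say that only the MBCP arm will be shown. The pillar speaks of the effects, and the Aims define the effects of MBCP as those compared with FoCC. This stands in part: a reader might infer that the plan forbids a comparison with FoCC, and the text does not support that. Still, the section does state a method for this conclusion, and the benchmark it names is a norm.

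Second, a reader might infer that this step drives the dissemination advice. The wording is softer: it informs and gives perspective, with no threshold or decision rule. Efficacy is judged by the time-by-condition interaction and cost-effectiveness is incremental. This stands.

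Third, a reader might take the 13 % to 26 % of high-scoring women who cross below 66 as a measure of false benefit. They are not that. Under a constant correlation they are cancelled by women crossing the other way. They would mislead only if responders were counted among women above the norm at T1. The section does not say so, nor does it say that 66 is the norm. This stands too.

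Fourth, selection is on W-DEQ-A alone, so other measures regress only as far as they correlate with it.

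Finally, FoCC is an upgraded, active programme. A null difference from it would not show that MBCP brings no benefit, and comparing end scores with norms is a legitimate description. The norm comparison should therefore be kept.

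**Conclusion.** The point holds in a limited form. As written, the clinical significance of MBCP is judged without the control arm that the trial already has. Natural change, concurrent care and attention between T1 and T2 would then be credited to MBCP. This is the firm part; it rests on the text alone, and its size cannot be derived from the document.

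Regression to the mean is a possible addition for W-DEQ-A and correlated measures. From T1 to T2 its net size is zero under a constant correlation. It is about 0.23 to 0.34 population SD (7 to 11 points) under the assumed decay from 0.9 to 0.8 or 0.7, with normal scores and a top-25 % source population. It is smaller if the source pool is already more fearful. The documents do not show which case applies, so a general claim that regression to the mean inflates this pillar is not supported.

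The controlled primary analysis and the sample size are unaffected. The change is worth making because it protects the clinical conclusion at almost no cost.

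**What to change.** In the Dissemination recommendation section:

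1. Report pre- and post-treatment scores against the norms for MBCP and FoCC side by side. Keep the within-MBCP figures as description.
2. Base any statement of clinical significance over FoCC on the MBCP-minus-FoCC difference at T2, adjusted for the T1 score, with a 95 % CI. For W-DEQ-A, give both the score difference and the difference in the share below the trial's own cut of 66, so that the conclusion does not hang on a dichotomy.
3. State that FoCC is an active comparator, so a null difference does not show the absence of any benefit.

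This costs one sentence in the plan and one extra regression. The scores are already collected in both arms and no change in sample size is needed. The reported clinical benefit may look smaller.

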## Discussion

This will be the first RCT comparing the effects of MBCP to FoCC on an array of childbirth and early parenting outcomes in pregnant women with a high level of FoC and their partners. This study will provide greater insight into the psychological processes underlying the occurrence, development and responses to FoC. Given the high prevalence and severe negative impact of FoC for pregnant women and their infants, this study can be of major importance if statistically and clinically meaningful benefits are found. Addressing the problem of FoC is critical and the proposed study evaluates an innovative MBCP that holds the potential of being an effective, non-invasive, and non-medical intervention for pregnant women with FoC, whit the potential for widespread dissemination that builds on the popularity of MBP’s. Further, we expect a potentially stronger effect of MBCP than FoCC on adaptation to the perinatal period, and a decrease in not-urgent medical interventions during childbirth. A reduction in unnecessary medical interventions has the potential to reduce or redirect the costs of midwifery care towards a more preventive approach for women and their partners in the perinatal period.

Some limitations to this study design need to be considered. First, the quasi-experimental study design creates less homogeneous groups then with full randomization (RCT) and permits a greater risk of bias due to potential alternation and allocation problems. To work with this, we adopted the recommendations for designing the Q-RCT studies from the Cochrane Handbook for Systematic Reviews of Interventions [86]. Due to the steadily increasing gestational age, dependency on recruitment speed and efficiency, and the required size of approximately six participants in the intervention group, we are obliged to use the quasi-randomization procedure in order to be able to conduct this study efficiently. A second limitation is the uncertainty of the power of this study due to the unknown effect size of the comparison group. To cover this limitation, we have chosen to downsize the expected large effect size of MBCP as shown in Duncan and [name]’s [40] study to a medium effect size in order to not under-power our study. An additional limitation is the potentially sizable dropout of participants due to their possibly strong preferences for one of the study’s interventions, the nine weeks duration of the programmes, and the relatively long and direct follow up after the birth. As a retention strategy we provide the participants with a financial incentive (€50) for completing the measurements following the birth.

Among the strengths of this study are the clinical-based experimental design, the extensive cognitive-emotional and behavioural measurements in pregnant women and their partners during the entire perinatal period, and the representativeness of the study sample as well as the generalizability of the study’s results. The complex and innovative measurements of FoC in this study are an important strength in research on FoC not only in pregnant women but also in their partners.

In the future, it would be interesting to evaluate the effects of MBCP on the physiological pathways of the stress response, such as the hypothalamic–pituitary–adrenal (HPA) axis, and maternal and foetal levels of corticosteroids in relation to perinatal outcomes for mother and baby. A study of the implementation and dissemination of MBCP into midwifery practice in the Netherlands would be the next logical step in MBCP research. Future research on the effects of mindful parenting on the mother-infant relationship, assessments of infant emotional expression and regulation, and stress due to fear, anxiety or depression in new mothers will allow for continuity between research and treatment for women at risk.

With this study we also aim to increase awareness among maternity caregivers of the important effects of maternal psychological wellbeing during the processes of adaptation to pregnancy, childbirth and parenting. Findings from this study would help midwives in their role of signalling, referring, cooperating with psychologists and preparing expectant women and their partners who are experiencing consequences of FoC in pregnancy, during childbirth and in parenting. Midwives are an ideal group of professionals to incorporate MBCP into their midwifery practices in The Netherlands for prevention and co- treatment purposes, because of the frequent and intimate contact with pregnant women and new families.

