### Mechanisms of action and process evaluation

Changes in overall mindful awareness, self-compassion, and catastrophic beliefs are hypothesised to be potential underlying working mechanisms of MBCP leading to positive changes in mental health and behaviour during the perinatal period. Overall mindful awareness including qualities such as observing, describing, acting with awareness, non-judging and non-reactivity to inner experience, will be assessed by the Five Facet Mindfulness Questionnaire (FFMQ) [81]. In addition, mindful awareness specifically related to one’s role as a (new) parent will be assessed with the Interpersonal Mindfulness in Parenting Scale (IM-P) [82]. Self-compassion will be assessed by the Self-Compassion Scale-Short Form (SCS- SF) [83], and catastrophic beliefs will be assessed by the Perinatal Disaster Scenarios Scale (PDSS).

Expectancy effects in women and partners will be assessed by the question: “If you had a choice, which one of the study’s programmes would you prefer to participate in?”. Adherence to MBCP will be assessed by number of classes attended and weekly diaries of the number of minutes spent in formal meditation practice each week between sessions. Data regarding the number of attended sessions of FoCC will also be collected.

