### Statistical analyses

#### Primary analyses

Dichotomous outcome data will be analysed using Chi-square tests or logistic regression using the method of ‘last observation carried forward’ (i.e., assuming no change) to handle dichotomous incomplete data. Continuous outcome data will be analysed with Multi-level analyses. Multi-level analyses with full information maximum likelihood (FIML) estimation use all available data and allow intention-to-treat analyses including all participants with incomplete data and participants who dropped out during the study. Continuous variables will be transformed into *Z*-scores. In this way, the parameter estimates can be interpreted as a measure of effect: i.e., as Cohen’s *d* for dichotomous predictors and as *r* for continuous predictors. Outliers will be identified. Analyses will be run twice: once in which all original scores will be included and once in which outliers will be changed to *Z*-scores (-) 3.29. Dependent variables will be level of FoC, labour pain and willingness to accept obstetrical interventions without medical indications. Predictors will be the different time measurements (T2, T3, and T4 against T1) and condition (MBCP versus FoCC). Interaction effects of time X condition will be added to the model to examine which programme is more effective over time.

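### The likelihood model that handles dropout omits programme preference, which the protocol names as one possible cause of dropout and already records

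*Protocol article*

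**What the plan says.** The Discussion names a "potentially sizable dropout of participants due to their possibly strong preferences for one of" the two interventions. Two further causes stand beside it: "the nine weeks duration of the programmes, and the relatively long and direct follow up after the birth". The remedy given there is an incentive: "As a retention strategy we provide the participants with a financial incentive (€50) for completing the measurements following the birth".

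The section on mechanisms of action and process evaluation records programme preference with one item for women and partners. It introduces the item thus: "Expectancy effects in women and partners will be assessed by the question". No time for it is given there, and it does not appear in Table 4.

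Under Primary analyses, continuous outcomes are analysed by multi-level models with FIML, which are said to "use all available data and allow intention-to-treat analyses including all participants with incomplete data and participants who dropped out during the study". The model terms are stated: "Predictors will be the different time measurements (T2, T3, and T4 against T1) and condition (MBCP versus FoCC"), followed by "Interaction effects of time X condition will be added to the model to examine which programme is more effective over time". Preference is not among them, and no other described analysis uses it.

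**The concern.** FIML handles dropout correctly if, given what is in the model, leaving does not depend on the unseen outcome. Here the model contains arm, time and the scores observed so far. A woman who leaves before T2 still contributes her T1 score, but her later course is inferred from women in the same arm with similar scores who stayed.

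That inference goes wrong if leavers and stayers differ in preference, and preference also predicts how fear or pain changes beyond baseline and arm. The two arms could then lose different kinds of women: those wanting MBCP from the FoCC arm, and those wanting FoCC from the MBCP arm. The time-by-condition contrast would carry part of that difference. At stake is the primary comparison, through a mechanism that the authors themselves foresee and have an item to measure.

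**Working it through.** **Yardstick.** The plan gives no dropout rate and no preference split, so no figure of its own can be reproduced for this point. Its sample size does reproduce. With correlation 0.5, the SD of change is √(2(1 − 0.5)) = 1. With d = 0.5 (the article says only medium), two-sided 5% alpha and 80% power, n per arm = 2(1.96 + 0.842)²/0.5² = 62.8, so 63. The exact t-test gives 63.8, so 64 per arm and 128 in total, as stated. An effect of 0.5 SD is therefore a fair yardstick.

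**Inputs, all assumed.** p is the share preferring MBCP. Dropout is a when the allocated programme is the preferred one and b when it is not. q is the difference in T2 outcome, in SD and given T1 and arm, between women who prefer MBCP and the others.

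**Formulas.** Share preferring MBCP among those retained:
- FoCC arm: S_F = p(1 − b) / [p(1 − b) + (1 − p)(1 − a)]
- MBCP arm: S_M = p(1 − a) / [p(1 − a) + (1 − p)(1 − b)]

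If preference is prognostic in both arms, bias in the contrast ≈ (S_M − S_F) × q.

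**Dropout in FoCC only.** p = 0.6, a = 0.10.
- b = 0.30: S_F = 0.42/0.78 = 0.538, a fall of 0.062.
- b = 0.40: S_F = 0.36/0.72 = 0.50, a fall of 0.10.
- With q from 0.3 to 0.8 SD, the FoCC mean is off by 0.062 × 0.3 = 0.02 up to 0.10 × 0.8 = 0.08 SD.

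**Mismatch dropout in both arms.** a = 0.10, b = 0.50.
- p = 0.7: S_F = 0.35/0.62 = 0.565 and S_M = 0.63/0.78 = 0.808, a gap of 0.243. With q = 0.3 to 0.5, the bias is 0.07 to 0.12 SD, or about 14% to 24% of 0.5 SD.
- p = 0.5: S_F = 0.25/0.70 = 0.357 and S_M = 0.45/0.70 = 0.643, a gap of 0.286. With q = 0.3, the bias is 0.09 SD.

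**Simulation of the T1/T2 likelihood model.** 400,000 women per arm, correlation 0.5, a = 0.10, b = 0.50. The last row has a different true contrast because mismatch itself worsens the outcome.

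| p | Role of preference | True contrast | Model without preference | Model with preference |
|---|---|---|---|---|
| 0.7 | none | −0.50 | −0.50 | −0.50 |
| 0.7 | q = +0.3 | −0.50 | −0.43 | −0.50 |
| 0.7 | q = +0.5 | −0.50 | −0.38 | −0.50 |
| 0.7 | q = −0.3 | −0.50 | −0.57 | −0.50 |
| 0.5 | q = +0.3 | −0.50 | −0.41 | −0.50 |
| 0.7 | mismatch shifts outcome by 0.3 | −0.62 | −0.61 | −0.62 |

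The model with preference was fitted separately by arm. Where the preference effect is the same in both arms (the q rows), a single preference-by-time term is already the correct model, so no three-way interaction is needed there.

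**Why mismatch alone does little.** Both arms then lose mismatched women. At p = 0.7, the mismatched share falls by 0.700 − 0.565 = 0.135 in FoCC and by 0.300 − 0.192 = 0.108 in MBCP. The net difference is 0.027, and 0.027 × 0.3 = 0.008 SD.

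**The case against.** The strongest reply is that a condensed article need not list auxiliary variables or sensitivity analyses, and that an analysis plan may contain them. It stands in part: nothing excludes such additions. But the article does not leave the model open. It states the terms and rests its handling of dropout on that model, so the stated model can be judged.

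Several stronger readings are tempting and are not supported:
- A reader might infer that the protocol expects sizable dropout driven by preference. It says potentially sizable and possibly strong, and names two other causes.
- A reader might infer that the FIML analysis is biased. Bias needs preference to be prognostic beyond baseline, earlier scores and arm, and the documents do not say that it is. Nor does the article claim freedom from bias under informative dropout.
- A reader might infer that the loss falls mainly on FoCC. Nine group classes against two consultations makes a majority wanting MBCP plausible, but nothing documents it.
- A reader might infer that the question is asked after allocation. The time is simply not stated. The abbreviation list includes programme preferences, and the flow chart (Fig. 2), not readable here, may show when they are recorded.

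On size, the objection is fair. The upper values use 50% against 10% dropout, which is severe, and even 0.12 SD is below the standard error of d at 64 per arm, √(2/64) = 0.18. A full three-way model would also be costly. With three preference categories and four waves it adds 2 + 6 + 2 + 6 = 16 parameters per outcome. If 60% prefer MBCP and the rest split evenly, the smaller cells hold about 64 × 0.2 ≈ 13 women per arm before dropout. That argues against the full interaction, not against using preference at all.

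**Conclusion.** The point holds in a conditional form. The protocol names a possible cause of dropout, records it, and specifies a likelihood model that does not condition on it. If preference predicts both leaving and change beyond baseline and arm, missing at random fails in that model and the arm contrast is biased.

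The documents fix neither size nor direction. Under the assumed inputs above, the bias is about 0 when preference is not prognostic, about 0.01 SD when only mismatch matters, and up to about 0.12 SD when preference is prognostic and mismatch dropout is heavy in both arms. It can understate or overstate the MBCP effect. This is a modest, inexpensive improvement to the primary analysis. It is not evidence that the planned analysis is invalid.

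**What to change.** 1. State that the existing preference question is asked once before allocation is known. An answer given later may reflect the arm received and could not serve as a baseline variable.
2. Include the woman's answer in the FIML models for the continuous primary outcomes, either as an auxiliary variable or as a baseline covariate with its time interaction. Do not add the full preference-by-time-by-condition interaction. The time-by-condition terms then remain the arm contrast.
3. Report dropout by arm and by whether the allocated programme matched the stated preference, so that readers can see if the mechanism operated.

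Cost: fixing when one existing question is asked, some analysis wording, and a few parameters per outcome. As a covariate with four waves this is 1 + 3 = 4 if preference has two categories and 2 + 6 = 8 if it has three. No new instrument, visit or participant is needed. The change does not protect against dropout that depends on unobserved outcomes for other reasons.
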